## Abstract

**Background:**

The diagnosis and management of bipolar disorder are limited by the absence of available biomarkers. Patients with bipolar disorder frequently present with mood instability even during remission, which is likely associated with the risk of relapse, impaired functioning, and suicidal behavior, indicating that the illness is active.

**Objective:**

This research protocol aimed to investigate the correlations between clinically rated mood symptoms and mood/behavioral data automatically collected using the *Toi Même* app in patients with bipolar disorder presenting with different mood episodes. This study also aimed to assess the feasibility of this app for self-monitoring subjective and objective mood/behavior parameters in those patients.

**Methods:**

This open-label, nonrandomized trial will enroll 93 (31 depressive, 31 euthymic, and 31 hypomanic) adults diagnosed with bipolar disorder type I/II (Diagnostic and Statistical Manual of Mental Disorders, 5th edition criteria) and owning an iPhone. Clinical evaluations will be performed by psychiatrists at the baseline and after 2 weeks, 1 month, 2 months, and 3 months during the follow-up. Rather than only accessing the daily mood symptoms, the *Toi Même* app also integrates ecological momentary assessments through 2 gamified tests to assess cognition speed (QU*i*CKBRAIN) and affective responses (PLAY*i*MOTIONS) in real-life contexts, continuously measures daily motor activities (eg, number of steps, distance) using the smartphone’s motion sensors, and performs a comprehensive weekly assessment.

**Results:**

Recruitment began in April 2018 and the completion of the study is estimated to be in December 2021. As of April 2019, 25 participants were enrolled in the study. The first results are expected to be submitted for publication in 2020. This project has been funded by the Perception and Memory Unit of the Pasteur Institute (Paris) and it has received the final ethical/research approvals in April 2018 (ID-RCB: 2017-A02450-53).

**Conclusions:**

Our results will add to the evidence of exploring other alternatives toward a more integrated approach in the management of bipolar disorder, including digital phenotyping, to develop an ethical and clinically meaningful framework for investigating, diagnosing, and treating individuals at risk of developing bipolar disorder or currently experiencing bipolar disorder. Further prospective studies on the validity of automatically generated smartphone data are needed for better understanding the longitudinal pattern of mood instability in bipolar disorder as well as to establish the reliability, efficacy, and cost-effectiveness of such an app intervention for patients with bipolar disorder.

**Trial Registration:**

ClinicalTrials.gov NCT03508427; https://clinicaltrials.gov/ct2/show/NCT03508427

**International Registered Report Identifier (IRRID):**

DERR1-10.2196/18818

## Introduction

### Background

In clinical practice, the diagnosis and management of mood/behavioral symptoms in bipolar disorder rely on subjective information and clinician’s evaluations, thereby raising issues, including patient recall bias, decreased illness insight during acute affective episodes, and differences in clinical assessment experience [1]. In patients with bipolar disorder, mood changes are often accompanied by shifts in other behavioral patterns such as motor activity, energy, sleep, and cognitive functions [2]. In addition, many patients with bipolar disorder experience significant daily or weekly mood swings, which do not fulfill the criteria of an acute episode but are above the levels of mood/behavioral changes experienced by nonpsychiatrically ill individuals [3,4].

Mood instability in bipolar disorder increases the risk for relapse [5] and impairs daily functioning over time [6-8], indicating that the illness is still active. Evidence has shown that patients with bipolar disorder in remission who presented with emotional hyper-reactivity, which was assessed as a proxy of mood instability by using an analog self-rated scale, had significantly increased risk for cardiometabolic dysfunction and poor cognitive functioning [9,10]. A recent study using a smartphone-based mood self-monitoring in patients with bipolar disorder has shown that mood instability was associated with significantly increased perceived stress, decreased quality of life, and impaired functioning, although most of these patients were in remission during the 9-month study period [11]. These findings highlight that mood instability could provide unique additional variance in predicting bipolar illness activity. However, the longitudinal pattern of mood instability is poorly understood as it is difficult to assess validly [12,13]. Therefore, the ability to assess mood/behavior changes continuously in real time and in more ecological conditions may be an opportunity for better understanding the clinical progression of bipolar disorder and for monitoring individual treatment outcomes.

### Digital Phenotyping in Bipolar Disorder

Currently, more than 35% of the world’s adult population owns and uses a smartphone [14]. Smartphones offer the opportunity to collect a vast amount of objective, fine-grained information (eg, data on phone usage, voice features, GPS data) in real time, which may reflect behavioral patterns, thereby providing novel insights into physical and mental illnesses [15-17]. As stated by the World Health Organization, “the use of mobile and wireless technologies to support the achievement of health objectives (mobile health [mHealth]) has the potential to transform health service delivery across the globe” [18]. Different mHealth interventions have been developed and used for various medical conditions such as diabetes, cardiovascular disease, asthma, and headache [19]. In psychiatry, mHealth systems for depression, anxiety, eating disorders, schizophrenia, and bipolar disorder have been gaining traction [20-26].

Several studies have evaluated the possibility of providing remote mood monitoring for patients with bipolar disorder by using diverse digital technologies [27-37]. For example, the ChronoRecord study included daily mood charting by using a computer [36,37]. In the AMoSS (Automated Monitoring of Symptoms Severity) study, participants monitored their moods daily by using a study-specific smartphone app, and they completed their weekly mood measures by using the True Colours system [38] and by wearing movement-sensing devices to monitor multiple physiological parameters [37]. This study has demonstrated that mood and activity monitoring were well accepted and tolerated by the participants who also reported that mood monitoring assisted them in the early recognition of their mood states [34]. The MONARCA (MONitoring, treAtment and pRediCtion of bipolAr Disorder Episodes) studies showed correlations between the severity of depressive and manic symptoms self-reported by patients with bipolar disorder who were using an electronic device and the clinically rated symptoms measured using standard mood rating scales [16]. The OpenSIMPLe feasibility study, which used a smartphone-based psychoeducation program for bipolar disorder, reported high percentages of perceived helpfulness, well-being, and general health among all the participants [33]. Moodswings, an internet-based self-help program for bipolar disorder, which includes psychoeducational material and cognitive behavioral therapy elements, has reported significant reductions in mood symptoms and improvements in the quality of life and medication adherence in patients with bipolar disorder who were using this platform [27].

Despite the fast growing development of digital technologies and the excessive hype for their use in psychiatry, robust evidences in this emerging field are lacking. For example, compelling pilot results of many app studies have not translated into clinical practice [35,39]. Standardized methods to collect, analyze, and report digital mood/behavioral data as well as clear frameworks regarding privacy and security of data are still not available [40,41], making the implementation of feasibility and validation studies an important step of this process.

### Objectives of This Study

In order to tackle some of these questions as well as to contribute to the evidence on digital phenotyping in bipolar disorder, we developed the *Toi Même* mHealth platform, which comprises the *Toi Même* smartphone app to self-monitor subjective and objective parameters of bipolar illness activity. The name of this project was inspired by the foreword engraved on the frontispiece of the Temple of Delphi—“Know thyself” (ie, *Connais toi toi-même,* in French). This expression was adopted by the philosopher Socrates who uttered it in his dialogues with his mentor Platon: “Know thyself as the dweller of the mind, senses, and the body” [42]. Our research protocol was carried out in real-world clinical settings with patients with bipolar disorder and we aimed to investigate the correlations between the clinically rated mood symptoms and mood/behavioral data that were automatically collected using the *Toi Même* app in patients with bipolar disorder presenting with different mood episodes. This study also aimed to assess the feasibility of this app for self-monitoring subjective and objective mood/behavior parameters in these patients.

## Methods

### Study Design

This is an applied research study on digital technology, software development, and analysis of app feasibility through an open-label, prospective, and multicenter clinical trial. The 3 investigation centers involved in this study are The Therapeutic Center for Bipolar Disorder (Centre Thérapeutique de Jour-Troubles Bipolaires, CTPJ-TB), Clinique Bellevue, Meudon, France; Clinique du Château de Garches, Garches, France; and the Service Hospitalo-Universitaire GHU Sainte-Anne, Paris, France.

### Clinical Assessments

Data on sociodemographic and clinical assessments were performed at baseline and after 2 weeks, 1 month, 2 months, and 3 months. These are the time points at which clinical evaluation is routinely performed at the CTPJ-TB. Hence, the study assessments did not add any extra burden on the participants or extra contact time with the staff.

The severity of the depressive and manic symptoms was evaluated using the Montgomery-Åsberg Depression Rating Scale (MADRS) [43], a 10-item questionnaire, ranging from 0 to 60, with higher scores indicating more severe depression, and the Young Mania Rating Scale (YMRS) [44], a 11-item questionnaire, ranging from 0 to 60, with higher scores indicating severity of (hypo)manic symptoms. Overall functioning was assessed using the Functioning Assessment Short Test (FAST), which encompasses 24 items to evaluate 6 functional domains: autonomy, occupational functioning, financial issues, interpersonal relationships, leisure time, and cognitive functioning. FAST scores range from 0 to 72, and higher scores indicate poorer functioning and greater disability [8].

In addition to the clinical evaluations, participants completed self-report evaluations of mood symptoms, behavior, and sleep patterns by using validated instruments. Depressive and manic symptoms were self-assessed using the 16-item Quick Inventory of Depressive Symptomatology Self-Report (QIDS-SR) [45] and the Altman Self-Rating Mania, a 5-item scale [46], respectively. Sleep patterns were assessed using the Pittsburgh Sleep Quality Index [47], which differentiates “poor” from “good” sleep by assessing 7 sleep domains, that is, quality, latency, duration, habitual sleep efficiency, sleep disturbances, use of sleep medication, and daytime dysfunction. A global score of 5 or greater indicates sleep disturbances. Levels of activation were measured using the Multidimensional Assessment of Thymic States, a 20-item self-report instrument that assesses the levels of activation uncoupled from mood during the preceding week [48]. It quantitatively evaluates 5 dimensions, namely, emotional reactivity, sensory perception, psychomotor activity, motivation, and cognition, each of which can vary from hypoactivation to hyperactivation [7]. At the end of each evaluation, the investigators asked patients to give feedback regarding the overall satisfaction, ease of use, and perceived helpfulness of the *Toi Même* app (ranging from 1=not at all to 5=extremely).

The clinical data were collected using the Research Electronic Data Capture (REDCap) software [49], which is a widely used data collection platform. REDCap follows the international rules for validation, qualification, and security gold standards, which are also aligned with the Pasteur Institute’s privacy/security rules for data collection.

### *Toi Même* App

Rather than only accessing the categories of mood symptoms, the *Toi Même* app expands on the existing digital self-assessments for bipolar disorder by integrating ecological momentary assessments of the fundamental dimensions of behaviors (eg, motor activity, cognition, affective response) in the same tool through 2 gamified tests, which were created and adapted by the first author ([name]) in order to assess cognition speed (QU*i*CKBRAIN) and affective responses (PLAY*i*MOTIONS) in real-life contexts. These games also passively collect data regarding user’s response time (seconds) and the number of hits/errors in each game trial, continuously measure the daily motor activities (eg, number of steps, distance) using the smartphone’s motion sensors, and perform a comprehensive weekly assessment, including validated self-rating scales [45,46,48]. Moreover, this app is special because *Toi Même* is the first app developed in France without commercial purposes, and it has been developed specifically for monitoring bipolar illness activity.

The principles, content, and the specifications of the *Toi Même* app were conceived by [name]. After a year of collaborative work among psychiatrists, neuroscientists, software engineers, and designers, the *Toi Même* app 1.0 version used in this study was available in French and was free of charge for the study participants. The information technology department of Pasteur Institute provided all the technical support for coding the app and the platform’s back office. The *Toi Même* app functionalities are intended to be minimally invasive to the users’ daily routine and normal smartphone usage. After the patients were included in the study, patients received an email with a link to install the *Toi Même* app in their own smartphones. Once the app was installed, users could configure it to receive a notification to perform their daily/weekly assessments. The system automatically sends a reminder notification once if the users have not completed their assessments. The app allows collecting mood/behavior information in both active (ie, need the user’s action) and passive ways (ie, without the user’s action), which is captured using the smartphone sensors. Once a day, the app prompts the user to score a short graphic 8-item test, including the assessment of subjective levels of mood, energy, emotion, irritability, anxiety, motor activity, speech, and thought speed on a scale from –3 to +3. Sleep time (hours), daily events (yes/no), and medication intake (yes/no) are also assessed daily. The app also randomly delivers to the users each one of the games twice a week.

The game QU*i*CKBRAIN randomly offers a series of 7 trials, each one containing a pair of word image or a simple calculation. The user’s action is to analyze and answer if the word matches (or not) with the image (Figure 1A) or in case a calculation is presented, the user must answer if the result of the calculation is correct (or not) (Figure 1B). Correct and incorrect buttons are present in each trial. The QU*i*CKBRAIN task contains about 1000 different trials.

The game PLAY*i*MOTIONS is intended to assess the user’s affective response to the images. This test comprises about 1000 color images depicting a broad spectrum of themes, including humans, animals, objects, and scenes along with normative ratings on the affective/valence dimension (ie, the degree of positive, neutral, or negative affective response that the image evokes). In each game trial, an image appears on the smartphone screen for approximately 5 seconds (Figure 2A). Thereafter, the image fades away, after which a colored circle and 2 buttons appear: one button contains the name of the color of the circle written in the same color (or in a different color) as that of the circle and another button contains the name of a color different from that of the color of the circle. In this task, the user’s action is to analyze the 2 options offered and choose the one that corresponds with the color of the circle displayed on the screen (Figure 2B).

At the end of the daily assessment, the *Toi Même* app provides an intuitive dashboard reflecting some of the daily scores, the user’s mood/behavioral patterns during the last 7 days and, by data push, during the last 30 days (Figure 3). No diagnostic or therapeutic feedbacks are provided. All data recorded by the app are encrypted, synchronized, and stored in a deidentified format within the *Toi Même* server.

**Figure 1 figure1:**
[figure not shown]
Example of a cognitive speed assessment by the QU*i*CKBRAIN task.

**Figure 2 figure2:**
[figure not shown]
Example of an affective response assessment by the PLAY*i*MOTIONS task.

**Figure 3 figure3:**
[figure not shown]
Example of the *Toi Même* app dashboard.

### Outcome Measures

Outcome measures are assessed at the baseline visit and after 2 weeks, 1 month, 2 months, and 3 months [50]. Briefly, primary outcome measures focus on changes in the severity of the depressive and manic symptoms assessed using the MADRS and YMRS. Secondary outcomes include changes in the self-rated mood/behavioral symptoms and medication adherence assessed using the self-report instruments QIDS-SR, Altman Self-Rating Mania, Multidimensional Assessment of Thymic States, and the Medication Adherence Rating Scale [51]. Functioning will be assessed using the FAST scale. Feasibility measures include the proportion of eligible participants who have consented to participate in the study, the frequency of self-assessments, and the proportion of participants who continued using *Toi Même* app during the study period. The participant’s physical activity will be inferred using the number of steps and distance automatically captured by the smartphone motion sensors.

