### Sample Size

Considering that the focus of this pilot study is to have patients with bipolar disorder in different mood states (depression, euthymia, and hypomania), a conservative approach for calculating the sample size was adopted (ie, concordant pairs) to ensure more qualitative feedback [52]. The overall mood/behavior states assessed using the *Toi Même* app encompasses 8 dimensions of behavior (ie, mood, energy, emotion, irritability, anxiety, activity, speech, and thought speed). Each of these dimensions is rated using a score ranging from –3 to +3, yielding a total score of 24. Accordingly, a concordant pair between the app measurements and the clinical assessments of mood symptoms was defined as follows: (1) depression, a score of <–8 in the app assessments and scores of >15 for MADRS and <8 for YMRS; (2) euthymia, a score between –8 and +8 in the app assessments and scores of <15 for MADRS and <8 for YMRS; (3) (hypo)mania, a score of >+8 in the app and scores of <15 for MADRS and >8 for YMRS. Assuming that the expected proportion of the concordant pairs is 98%, with an estimated precision of 5% and a two-sided 95% CI, 31 patients will be included in each of the 3 groups to fully accomplish the study goals (N=93).

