### Statistical Analysis

Descriptive analyses will be conducted to characterize the sociodemographic and clinical characteristics of the initial sample as well as the retention at the end of the study. Receiver operating characteristics analysis will be applied to calculate the concordance ratio of the pairs (ie, the area under the curve) [53]. Given that patients have started using the app from the baseline visit, the clinical data collected at this time point will not be included in the concordant pairs’ analysis. Compliance will be calculated as the proportion of the enrolled patients completing the first 15 and then 30 and 90 consecutive days of ratings. The app completion rate would be completing at least 70% of the momentary assessments during the time a participant has continued in the study. The average ratings of the perceived helpfulness, ease of use, and overall satisfaction would be at least 3 on the 1 to 5 rating scores. Cluster analysis will be performed using principal component analysis (PCA) to identify groupings of the daily *Toi Même* mood/behavior questions. The PCA results will be then used to obtain a single summary statistic (*TM*P1) that will account for the maximum amount of variability in the 8 daily *Toi Même* mood/behavior responses across all the subjects during the study period. The summary statistic produced from the PCA-*TM*P1 will be used as a response to test for differences between groups in daily ratings and for comparison between this app score and the clinical rating scores. To test for differences between groups over time, linear mixed regression models will be used with autoregressive covariance adjustments for repeated measurements of continuous outcomes and logistic generalized estimating equations will be used for binary outcomes. In both linear and logistic generalized estimating equation models, adjustments for sex, age, day of the week, and elapsed time in the study will be included as other covariates in the models. The regularity in the daily ratings for each subject will be estimated using the root mean squared successive differences (a measure of the variability of the changes in scores over time), the Teager-Kaiser Energy Operator, which combines amplitude and frequency, and the information entropy, which measures regularity of amplitude [37]. The within-subject sample variance will be also used as a measure of regularity for each subject’s response and will estimate the distribution of the amplitudes recorded over time. Data analysis will employ the intention-to-treat principle by including all participants in the analyses, which will be conducted using the R programming language (R Core Team).

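### The named primary outcome, change in MADRS and YMRS, contains no app data: it cannot answer the stated objective and is not the quantity the sample size rests on

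*Protocol article*

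**What the plan says.** Four parts of the protocol article bear on this point.

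- **Objective** (Abstract; repeated under Objectives of This Study). The protocol "aimed to investigate the correlations between clinically rated mood symptoms and mood/behavioral data automatically collected using the" app, and has feasibility of the app as a second aim.
- **Outcome Measures.** The "primary outcome measures focus on changes in the severity of the depressive and manic symptoms assessed using the MADRS and YMRS". Self-rated symptoms and medication adherence are secondary. Functioning and feasibility measures follow without a rank. Neither correlation nor concordance between app and clinician appears in the list.
- **Sample Size.** Here "a concordant pair between the app measurements and the clinical assessments of mood symptoms was defined as follows", using bands of the app total score set against MADRS and YMRS cut-offs. The inputs are "Assuming that the expected proportion of the concordant pairs is 98"%, "with an estimated precision of 5% and a two-sided 95% CI", and the result is that "31 patients will be included in each of the 3 groups to fully accomplish the study goals (N=93").
- **Statistical Analysis.** "Receiver operating characteristics analysis will be applied to calculate the concordance ratio of the pairs", expressed as the area under the curve. Baseline clinical data are left out of that analysis. A summary app score from the principal component analysis is compared with the clinical ratings, and mixed models test differences between groups over time. No analysis of MADRS or YMRS change is named as primary.

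On design, the Abstract states: "This open-label, nonrandomized trial will enroll 93 (31 depressive, 31 euthymic, and 31 hypomanic) adults".

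**The concern.** The primary outcome should be the quantity that answers the main question and that the study was sized to estimate. Here the objective, the sample size and the concordance analysis all concern the relation between app and clinician. The Outcome Measures section alone points elsewhere, to change in two clinician scales.

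Followed as written, the primary outcome could be reported in full without using a single app measurement, while the question the study was built for would rest on analyses with no declared rank. Change in MADRS or YMRS is also hard to interpret in this design. There is no comparison group without the app, patients enter in a given mood state, and visits follow routine care at a treatment centre. Natural course, treatment and regression to the mean would all move the scores.

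**Working it through.** **1. The plan's own figure.** Inputs from Sample Size: expected proportion p = 0.98, precision d = 0.05, two-sided 95% interval (z = 1.96).

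n = z² × p(1 − p) / d² = 1.96² × 0.98 × 0.02 / 0.05² = 30.12, rounded up to 31 per group; 3 × 31 = 93.

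This reproduces the stated size exactly. A one-sided z gives 21.2, and reading 5% as the full interval width gives 120.5, so the two-sided half-width reading is the one used. The calculation treats each patient as one observation.

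**2. What the calculation covers.** Only the concordant proportion enters it. At p = 0.98 the half-width is 1.96 × √(0.98 × 0.02 / 31) = 4.9 points per group, and 2.8 points with all 93. No effect size, SD, power or alpha for MADRS or YMRS change is given, so the named primary outcome has no sample size that could be checked. For illustration only, assuming 80% power and a two-sided 5% test, 31 patients detect a within-group mean change of (1.96 + 0.84) / √31 = 0.50 SD of the change score. The protocol does not say whether that is enough.

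**3. Which sections agree.**

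| Section | Quantity | App data? |
|---|---|---|
| Objective | Correlation of app data with clinician ratings | Yes |
| Sample Size | Proportion of concordant pairs | Yes |
| Statistical Analysis | ROC area for the pairs; app summary score against clinical ratings | Yes |
| Outcome Measures (primary) | Change in MADRS and YMRS | No |

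The baseline rule sharpens the difference. Baseline clinical data are excluded from the concordance analysis, whereas baseline is the natural reference for any change score.

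**4. Can change be attributed to the app?** Without a comparison group, no. As an illustration, suppose normal scores, no true change, and a group that is the upper third at baseline. The expected change in SD units is −(1 − r) × 1.09, where r is the correlation between visits and 1.09 is the mean of the upper third of a standard normal:

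- r = 0.9: −0.11
- r = 0.8: −0.22
- r = 0.7: −0.33
- r = 0.5: −0.55

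Taking the selected share from one half to one quarter widens the range to −0.08 to −0.64. None of these inputs is in the protocol. They show direction and order of size only.

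**5. Does the stated size fit concordance as primary?** Yes, with one pair per patient: that is the calculation in step 1. With all four post-baseline visits there are up to 31 × 4 = 124 pairs per group, but they are not independent, and the simple formula no longer gives the interval.

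**The case against.** The strongest defence is that the Outcome Measures paragraph announces itself as a summary, cites a further source, and may simply be listing the clinical reference scales. The same two scales define the concordant pair, and the app-clinician analyses are specified and sized elsewhere. The study also calls itself a pilot. It stands that only this one section is out of line and that the remaining plan is coherent. It does not remove the contradiction: a summary may leave out detail, but this one names a different primary quantity, and nothing shown ties MADRS or YMRS change to app data.

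Four stronger readings are tempting and are not supported.

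- *The headline result will be a pooled before-after fall.* Statistical Analysis plans no such analysis; its models concern differences between groups over time.
- *The authors claim a treatment effect.* The Discussion presents the app as a stand-alone self-assessment instrument, the app description says users receive neither diagnoses nor treatment advice, and the Abstract leaves efficacy to later studies. The intention-to-treat wording could encourage such a reading but does not make the claim. For a study of correlation and feasibility, the lack of a control group is no fault in itself.
- *The registered primary outcome is wrong.* The article gives only the registration number; the registered wording is not available here.
- *Regression to the mean will produce a fall of a known number of points.* The protocol gives no entry mean, long-run mean or between-visit correlation.

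It is also fair to say that naming concordance as primary is not quite enough. The calculation assumes one observation per patient, the planned analysis is an area under the curve and not a proportion, and the concordance classes leave out a MADRS of exactly 15, a YMRS of exactly 8, and both scales raised together. The fix has to deal with these.

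**Conclusion.** The point holds as an inconsistency between the primary outcome and the rest of the plan. The named primary outcome contains no app data and cannot answer the stated objective, and the 31 per group (93 in total) derives wholly from a quantity that Outcome Measures does not list. This rests on the protocol's own wording and on arithmetic that reproduces exactly; no outside assumption is needed.

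That MADRS or YMRS change cannot be attributed to the app follows from the design. The regression-to-the-mean figures are illustrations and do not carry the conclusion. The two scales remain suitable as the clinical reference within the concordance measure; the fault lies in making their change primary.

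The sample-size arithmetic is correct, but its precision depends on the 98% assumption. With 30 of 31 pairs concordant the exact 95% interval is 83.3% to 99.9%, and at 90% concordance the half-width with 31 patients would be 10.6 points. That is a separate caution and does not alter this finding.

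**What to change.** 1. **Outcome Measures.** Name the proportion of app-clinician concordant pairs as the primary outcome. Either use one pair per patient at a single named post-baseline visit, which matches the sample-size calculation, or use all post-baseline visits with an interval that allows for clustering within patient. State how pairs that fall outside the three defined classes are counted.
2. **Statistical Analysis.** Report that proportion with its 95% CI as the primary analysis, and make the ROC area supportive.
3. **MADRS and YMRS change.** Move both to descriptive secondary outcomes, and state that no effect of the app is inferred from them.
4. **Optional secondary analysis.** Fit a mixed model of the app score on same-visit MADRS and YMRS, split into within-patient and between-patient parts, so that the association is not merely the spread created by recruiting three mood groups.

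The cost is a dated protocol amendment that gives its reason. It would be made during enrolment (25 of 93 patients by April 2019), so it should also say whether any concordance result had been seen. The app and clinician data are already planned. With one pair per patient, no change in sample size follows from the protocol's own inputs.
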